**Fig. 1 Fig1:**
[figure not shown]
PULSAR Specialist Care study design and planned timeline Notes. Indicated at the *bottom* is the study year. The two-step cluster randomise control trial is shown: half the clusters receive the intervention in step 1 and the remaining clusters receive the intervention in step 2. For a summary of the study evaluations see Table 1

**Table 1 Tab1:** Evaluation plan for the PULSAR Specialist Care study

	Sub-study name	Evaluation design	Unit of analysis	Number	Number at each time point	Number in each cluster at each time point	Detectable differences		
							Primary outcome, QPR	Secondary outcome, WEMWBS	Secondary outcome, INSPIRE
cRCT (quantitative data)	Stream 1 (primary analysis)	cross-sectional cRCT (complete step-wedge)	Consumers (mail-out)	756	252 at baseline 252 at step 1 252 at step 2	18	6.34 (medium effect)	NA	NA
	Stream 2	pre- and post-intervention (incomplete step-wedge)	Consumers (interviews)	252 (stream 1 subset)	63 at baseline 126 at step 1 63 at step 2	9	7.68 (medium effect)	4.80 (medium effect)	7.72 (medium effect)
	Stream 3	longitudinal, (same participant, 12-mths apart pre- and post-intervention)	Consumers with diagnosis of psychosis (interviews)	88 (stream 2 subset)	44 at baseline & step 1 44 at step 1 & step 2	6–7	10.94 (medium-large effect)	6.84 (medium-large effect)	11.28 (medium-large effect)
Nested Qualitative study (qualitative data)			Consumers Staff	20–24 20–24	10–12 at step 1 10–12 at step 2	Nested sub-study examining qualitative data collected in study interviews and focus groups			
Nested Process evaluation (both quantitative & qualitative data)			Consumers & staff	The process evaluation assesses a specific set of qualitative, quantitative and documentary data relating to each cluster.					

Notes. The primary analysis examines the primary outcome– the Questionnaire about the Process of Recovery (QPR) - collected in the two-step stepped-wedge cluster randomized controlled trial (cRCT). A subset of consumers in the cRCT participate in study interviews where secondary outcomes measuring well-being, service satisfaction and health economic impact are collected In a yet another subset in the cRCT, longitudinal data are collected via interviews that are 12 months apart from consumers with a diagnosis of a psychotic disorder. Qualitative and process evaluation sub-studies are nested within the overarching cRCT and include information from consumers and staff.

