#### Levels of consumer participation

In line with the presumption of capacity endorsed by the Victorian *Mental Health Act 2014* and research indicating that participating in research can lead to positive outcomes for people who experience mental health issues [28, 29], the project was designed to provide consumer participants with the opportunity to self-select into multiple levels of involvement. Consumers consenting to participation in the cRCT are offered three levels of involvement, see the three streams outlined in Table 1. In the cRCT stream 1, we collect primary outcome recovery-focused data from consumers recruited cross-sectionally via the mail at baseline (T0), end of year 1 (T1) and end of year 2 (T2), see Fig. 1. In the cRCT stream 2, we additionally collect secondary and other outcome data assessing mental health and wellbeing, service satisfaction, perceived coercion when accessing services, and health economic impact. This information is collected via face-to-face interviews from participants recruited cross-sectionally at pre or post-intervention. Stream 3 consists of a smaller subset of Stream 2 participants who have a clinical diagnosis of psychosis, e.g., schizophrenia, schizoaffective disorder, or bipolar disorder. Participants in this Stream provide longitudinal data via pre- and post-intervention face-to-face interviews. A pool of research assistants trained in study-specific interview procedures and blinded to intervention status, conduct all Stream 2 and 3 interviews. Consumers who volunteer for the nested qualitative sub-study do not need to participate in the cRCT. Consumer data from the cRCT and qualitative study may be used in the nested process evaluation.

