Other	‘Other’ measures that are listed as 9 to 15 in Table 4 above may be investigated as independent variables when relevant. For example, the primary outcome recovery (QPR) scores may be explored for associations with the individual-level scores on the Cohesion Ladder.
Cluster level	
Cluster group	Allocated to receive the intervention at either Step 1 or Step 2.
Intervention status (0/1)	A lag time of 6 months is anticipated until intervention effects are possible. The intervention status variable indicates that this lag time has passed.
Dosage (%)	Intervention dosage.
Time since intervention	All data are time-stamped in relation to the time the intervention was received at the cluster. Time value of “0” is given for the plus/minus 3 months from date of training; “1” for 4-to-6 months post training; “2” for 7-to-9 months post training, etc. Time value of “-1” for 4-to-6 months before training; “-2” for 7-to-9 months before training, etc.
Time	Study month that survey was completed: “1” = month 1, “2” = month 2, etc.
Cluster types - stratification variables, see Table 2	
Crisis assessment & treatment team	
Mobile support and treatment service or Community Care Unit	
Community Mental Health Service	
Continuing Care team	
PARC residential facility (Mind Australia)	
PARC residential facility (Ermha)	
Community outreach service	

Consumers participating in stream 3 who report having no contact with their mental health service in the previous 12 months do not complete measures pertaining to service evaluation (CSQ, MASS, Coercion Ladder: community services version, INSPIRE).

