### Sample size

The primary analysis examines QPR data from consumers in the cRCT (stream 1) and requires a total sample size of 756 consumers from 14 clusters over 3 years (see Table 1). This will be sufficient to detect a medium effect size representing a change in QPR score by 6.34, see Table 1. Secondary analyses that examine data from a subset of stream 1 consumers who participate in stream 2 of the cRCT, requires a total sample size of 252 consumers over the study period. This will be sufficient to detect medium effect sizes in the QPR and two secondary outcome measures (WEMWBS and INSPIRE), see Table 1. Additional secondary analyses to examine longitudinal data from a subset of stream 2 consumers who participate in stream 3 of the cRCT, requires a total sample size of 88 consumers over the study period. This will be sufficient to detect medium-large effect sizes in the QPR and WEMWBS and INSPIRE, see Table 1.

Sample size calculations were based on 14 clusters; intracluster correlation coefficient (ICC) of 0.05; significance level set at 0.05; power of 0.80; and available published [34, 36, 45] and unpublished (INSPIRE) data about distribution properties. All sample size calculations indicate the minimum number of participants we aim to recruit and were done using Stata statistical software *stepped-wedge* [46] Version 11, StataCorp. 2009.

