Participants who complete a face-to-face interview are required to provide full written informed consent for both the interview and to the researchers accessing routinely collected data using a revised PICF. Study interviews take around 60–90 min. At the end of T0 and T1 interviews, participants are asked whether they would be interested in completing a follow-up interview approximately 12 months later (for stream 3). If participants are willing to be contacted regarding the follow-up interview, they are asked to provide their contact details, give an indication of whether they are likely to relocate in the coming year, and provide the contact details of any friend or family member who might be able to pass on letters from the PULSAR project should they no longer be contactable. If participants are not available for a follow-up interview after re-contacting attempts have been made by the researchers, no additional data will be collected. Given that participants are the recipients of the intervention through services provided by trained specialist mental health care staff, no protocol for discontinued consumer participants is necessary.

All data are recorded on paper forms which are securely stored at the PULSAR administrative site. Procedures to ensure accuracy of data extraction include double entry from selected hard copy forms, range checks and examination of outliers.

For participants who provide Level 2 consent initially, then later all participants who complete a face-to-face interview, routinely collected medical data is extracted from organization-specific medical records, see Table 4. All identifiers are removed from the service record data and replaced with a code, enabling re-identification for the purpose of linkage with the participant’s interview data.

The privacy of all participants is safeguarded in accordance with the National Statement on Ethical Conduct in Human Research [47]. All data is stored on password protected computer systems located within the secure PULSAR administration site. The study data will be stored for a minimum of 7 years, after which time it may be destroyed. Re-identification codes are only accessible to the core research team responsible for data management. It is possible that participant data may be used in a non-identifiable format in future research.

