The analysis of data in a stepped-wedge cRCT is most suitably analysed in mixed-effects models [54]. The primary analysis examines the effect of PULSAR on the primary outcome (consumer-level QPR scores) using a linear mixed-effects model state ‘on an intention-to-treat basis’. The model will include intervention status and time as fixed effects and clusters and consumers as random effects. Normally step one is just to examine intervention – control group differences controlling for cluster, before including covariates. An a priori model-fitting analysis strategy will involve both univariate and multivariable models to be developed based on baseline consumer and cluster-level variables considered statistically significant (*p* < 0.10) or clinically important (e.g., age, sex), see Table 5, and included in the model as fixed. Model fit will be examined by comparing AIC values.

Secondary analyses will examine the effect of PULSAR on secondary outcomes (WEMWBS and INSPIRE) using a linear mixed-effects models to compare the intervention and control periods (pre-intervention).

Estimated intervention effects will be reported as the mean outcome difference for continuous outcomes and Odds Ratio for binary outcomes between intervention and control periods. This can be described as a meta-analysis approach as (in the case of continuous data) the mean change in each cluster will be standardized by using the variance of the outcome measure within that cluster. The estimated intervention effects will be reported with 95% Confidence Intervals and *p* values. Analysis will be conducted using Stata V.14, StataCorp. Stata Statistical Software: Release 14. College Station, TX: StataCorp LP, 2015.

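### Stream 3 on its own cannot separate the intervention from being a returning participant, because every control observation is a first interview and every intervention observation a second

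*Protocol article*

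**What the plan says.** Table 1 lists Stream 3 among the cRCT rows as "longitudinal, (same participant, 12-mths apart pre- and post-intervention", with "44 at baseline & step 1 44 at step 1 & step 2" and 6–7 people per cluster at each time point. It gives detectable differences of 10.94 (QPR), 6.84 (WEMWBS) and 11.28 (INSPIRE). Under Levels of consumer participation: "Participants in this Stream provide longitudinal data via pre- and post-intervention face-to-face interviews". The note to Fig. 1 says that "half the clusters receive the intervention in step 1 and the remaining clusters receive the intervention in step 2".

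Pairs are formed by re-invitation. Under cRCT data collection, people interviewed at T0 and T1 are "asked whether they would be interested in completing a follow-up interview approximately 12 months later (for stream 3". The Sample size section says of the 88: "This will be sufficient to detect medium-large effect sizes in the QPR and WEMWBS and INSPIRE, see Table 1".

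The model in the Main analysis plan is: "The model will include intervention status and time as fixed effects and clusters and consumers as random effects". No term for interview order is stated.

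Two rules bear on who is compared. Consumer selection criteria requires contact with a study cluster within 3 months of data collection. The text after Table 5 exempts "Consumers participating in stream 3 who report having no contact with their mental health service in the previous 12 months" from the service-evaluation measures, including INSPIRE.

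**The concern.** The first research question asks whether consumers in intervention clusters improve more than those under control. In Stream 3 nobody is described as interviewed twice under control, and nobody as first interviewed after the intervention. A difference between intervention and control observations is therefore also a difference between second and first interviews. What distinguishes a person interviewed again after 12 months from a new recruit includes having done the interview before, having been willing and traceable, having moved away from a recent service contact, and being a year further on.

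At stake is whether the Stream 3 results for QPR, WEMWBS and INSPIRE can be read as randomised evidence of an intervention effect, which their place in the cRCT rows of Table 1 invites.

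**Working it through.** **Layout.** 44/7 = 6.29 fits the stated 6–7 per cluster; 44/14 = 3.14 does not. Each group of 44 therefore comes from 7 clusters: the step-1 clusters give T0 (control) and T1 (intervention), and the step-2 clusters give T1 (control) and T2 (intervention).

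**Inputs.** From the Sample size section: 14 clusters, ICC 0.05, alpha 0.05 (two-sided assumed), power 0.80. The QPR SD is not given and is assumed to be 16. This is backed out from Stream 1: a stepped-wedge variance with fixed periods and random clusters, complete wedge, 18 per cell, gives 0.3964 SD, and 0.3964 × 16 = 6.342 against the stated 6.34.

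**Reproducing 10.94.** T0 and T2 each occur in one sequence only, so their period effects absorb those data and the intervention effect is identified from T1 alone:

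- SE = SD × √[(2/7) × (ICC + (1 − ICC)/m)]
- with m = 6: 16 × √[(2/7) × (0.05 + 0.95/6)] = 16 × 0.2440 = 3.90
- detectable difference = (1.960 + 0.842) × SE = 10.94, as stated

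The full generalised least squares calculation over both time points gives the same 10.936. In SD units this is 0.6835. An SD of 10 then gives 6.835 for WEMWBS (stated 6.84), and an SD of 16.5 gives 11.278 for INSPIRE (stated 11.28); both SDs are assumptions that fit. The agreement supports the inferred layout.

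**Aliasing.** Over the 28 cluster-by-period cells:

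| Fixed effects | Rank | Columns |
|---|---|---|
| 3 periods + intervention | 4 | 4 |
| 3 periods + intervention + interview order | 4 | 5 |
| 14 clusters + 2 periods + intervention | 16 | 17 |

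The stated kind of model is estimable (first row). Intervention and interview order cannot be told apart (second row). Once clusters are fixed the effect is not estimable (third row), so the within-person pairs add nothing that identifies it.

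**Size of the bias.** With no true intervention effect, second-interview shifts of 1, 3 and 5 points gave estimated intervention effects of exactly 1, 3 and 5, at within-person correlations of 0, 0.5 and 0.7. A pure calendar trend gave an estimate of 0.

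**Consequence for the test.** Take an illustrative shift δ of 0.2 to 0.3 SD, that is 3.2 to 4.8 points. The chance of a significant result is Φ(δ/SE − 1.96) + Φ(−δ/SE − 1.96).

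- δ = 3.2: δ/SE = 0.820, giving 0.127 + 0.003 = 0.13
- δ = 4.8: δ/SE = 1.230, giving 0.233 + 0.001 = 0.23

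For comparison, an uncontrolled paired test at within-person correlation 0.5 has SE = 16 × √[2 × (1 − 0.5)]/√88 = 1.706, and would give 0.47 to 0.80.

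**INSPIRE.** A new recruit must have had contact within 3 months. Skipping INSPIRE after 12 months without contact can in practice arise only at the second interview, which is always in the intervention condition.

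**The case against.** The strongest reply is that Stream 3 is not an uncontrolled before-and-after study. The stated model includes time, the effect is estimable, and it uses a concurrent T1 comparison between randomised sequences that removes shared calendar trend. This stands. A reader might infer that no effect can be estimated, or that secular trend drives it; the design does not support either. What the reply leaves open is that the T1 comparison sets returners against new recruits, which randomisation of clusters does not balance.

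A reader might also fault 10.94 for ignoring the pairing. That would be wrong: in the stated model the pairs carry no information about the intervention effect, and 10.94 is correct for it. It is a statement about precision and gives no protection against bias.

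It is tempting to say that the bias favours the intervention. The article does not show this. Entry needs no score threshold and participants select themselves, so people who volunteer when well could drift downward.

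The rates of 47–80% apply only to a paired test, which the article does not plan.

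Finally, a joint model of Streams 2 and 3 could break the aliasing, since Stream 2 includes post-intervention first interviews. This is fair, and the detail may sit in an analysis plan that is not shown. It does not change what the article itself fixes: the schedule, and separate detectable differences for Stream 3.

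**Conclusion.** The point holds for Stream 3 analysed on its own. Intervention status and interview order coincide for all 88 people, so any effect of being a returning participant enters the intervention estimate in full, in an unknown direction. INSPIRE has the further problem of being dropped selectively under the intervention.

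The aliasing rests only on the layout inferred from Table 1. The 13–23% also rests on an SD of 16, an ICC of 0.05, 6 per cell and an assumed shift of 3.2 to 4.8 points; at 44/7 per cell the SE is 3.84 and the range 13–24%. The within-person correlation does not affect these figures.

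It would go too far to extend this to the trial's main result. Stream 1 is cross-sectional and its primary analysis is unaffected; the Sample size section places Stream 3 among additional secondary analyses.

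**What to change.** 1. In Table 1 and the Sample size section, state that Stream 3 describes within-person change and does not by itself support an intervention effect. Remove its three detectable differences from the cRCT rows, or qualify them as precision figures that assume no effect of interview order or selective return.
2. Estimate WEMWBS and INSPIRE intervention effects from Stream 2 first interviews only, and keep Stream 3 second interviews out of the T1 comparison between sequences. Alternatively, model the two streams jointly with a term for interview order, which the post-intervention first interviews make estimable.

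The cost is a change of wording and of analysis set, and Stream 3 then supports a weaker claim. If the 63 + 126 + 63 = 252 Stream 2 consumers in Table 1 are distinct people, second interviews are additional to them and the change loses no planned Stream 2 data.

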### Explanation for choice of comparators

The design was developed to combine the rigor of a cluster randomized trial with the pragmatic approach of the stepped wedge design to implement and evaluate the intervention at all sites [20, 21, 24]. Control sites are those that are yet to receive the intervention. Since all sites eventually receive the intervention, data from sites in control phases will be compared with data from sites that have received the intervention. There are no study restrictions on the care provided in control phases. Treatment as usual is described later under the heading “Control”.

### Study setting and clusters

In Victoria, specialist mental health services include area-based clinical services comprising a range of teams and service types, in particular, inpatient units and community-based continuing care and treatment teams, as well as Mental Health Community Support Services (MHCSS) [25] that provide residential and outreach support. The study setting is the catchment of Monash Health, the largest public health care provider in Victoria, which provides services to a population of over 950,000 in the South-Eastern suburbs of Melbourne, and encompasses a greater population of 1.34 million people [26]. The Monash Health catchment area includes the City of Greater Dandenong, the most culturally diverse municipality in Victoria [27]. Three organisations that operate within the Monash Health catchment are involved in the study including: Monash Health Specialist Clinical Mental Health Services and, from the MHCSS sector, Mind Australia and Ermha.

Fourteen participating specialist mental health care clusters are spread over 18 adult community-based mental health service sites. See Table 2 for a description of study clusters.

### Participants

#### Levels of staff participation

Staff participate in the PULSAR training intervention but no data from individual staff members are collected as part of the cRCT. However, staff are requested to complete a training evaluation at the conclusion of the training and this data will be examined in the process evaluation sub-study. Staff may volunteer for the nested qualitative sub-study.

#### Staff selection criteria

Staff at the study clusters who receive the PULSAR training intervention must fulfil the following inclusion criteria: (a) working on a part-time or full-time basis within the team in a direct service capacity (and not employed on a casual basis); (b) have an active case load with consumers who are recruited into the evaluation. Staff are ineligible if they are also working in a non-intervention cluster at the time of training (to reduce risk of contamination). Similarly, staff are eligible to participate in the nested qualitative sub-study if currently working at services where the training intervention has been provided; and ineligible if they are either not working at a participating cluster site (even if they have completed the training) or no longer work in a direct service role.

#### Levels of consumer participation

In line with the presumption of capacity endorsed by the Victorian *Mental Health Act 2014* and research indicating that participating in research can lead to positive outcomes for people who experience mental health issues [28, 29], the project was designed to provide consumer participants with the opportunity to self-select into multiple levels of involvement. Consumers consenting to participation in the cRCT are offered three levels of involvement, see the three streams outlined in Table 1. In the cRCT stream 1, we collect primary outcome recovery-focused data from consumers recruited cross-sectionally via the mail at baseline (T0), end of year 1 (T1) and end of year 2 (T2), see Fig. 1. In the cRCT stream 2, we additionally collect secondary and other outcome data assessing mental health and wellbeing, service satisfaction, perceived coercion when accessing services, and health economic impact. This information is collected via face-to-face interviews from participants recruited cross-sectionally at pre or post-intervention. Stream 3 consists of a smaller subset of Stream 2 participants who have a clinical diagnosis of psychosis, e.g., schizophrenia, schizoaffective disorder, or bipolar disorder. Participants in this Stream provide longitudinal data via pre- and post-intervention face-to-face interviews. A pool of research assistants trained in study-specific interview procedures and blinded to intervention status, conduct all Stream 2 and 3 interviews. Consumers who volunteer for the nested qualitative sub-study do not need to participate in the cRCT. Consumer data from the cRCT and qualitative study may be used in the nested process evaluation.

